
## Methods/Design

Ethics approval for the **Omega-3 fatty acids (Fish Oils) **and **A**spirin in **V**ascular access **OU**tcomes in **RE**nal **D**isease (FAVOURED) trial has been obtained from several local Human Research Ethics Committees and will be obtained in all participating centres prior to study initiation and patient enrolment. The study will be performed in accordance with the 2000 Edinburgh, Scotland Revision of the Declaration of Helsinki, the National Health and Medical Research Committee (NHMRC) Statement on Human Experimentation, Joint NHMRC/AVCC Statement and Guidelines on Research Practice, applicable ICH guidelines and the Therapeutic Goods Administration (TGA). The trial has been registered with Australia & New Zealand Clinical Trials Register (ACTRN12607000569404).

### Study Design

This is a factorial-design trial, where patients are randomised to aspirin or matching placebo, and also to omega-3 fatty acids or matching placebo, resulting in four treatment groups (Figure 1). Randomisation will be achieved using a dynamic balancing method, balancing over the two stratification factors of 1) study site and 2) upper versus lower arm AVF.

**Figure 1 F1:**
[figure not shown]
**Schema for the FAVOURED Trial**.

Each of the two interventions will be studied using a matching placebo, in order to make this a double-blind trial. At the completion of treatment, patients and investigators will be asked which treatment they believe the patient has been receiving, in order to have a measure of the degree of effectiveness of blinding. Two independent observers will make the primary outcome of patency assessment, unaware of the patient's treatment assignment and treatment course or medical history.

### Patient Population

The study will be multi-centre, and open to all public and private hospital renal units that perform vascular access procedures. The study will be conducted in Australia and New Zealand. In the future international collaboration with sites in Asia and the United Kingdom will be considered.

Patients must meet the following inclusion and exclusion criteria:

#### Inclusion criteria include

The Study population will include adults with the following inclusion criteria:

1. Stage 4 or 5 Chronic Kidney Disease

2. Currently on haemodialysis or haemodialysis is planned to start within 6 months (including patients currently on peritoneal dialysis).

3. Planned AVF will be the primary haemodialysis access mechanism.

4. Surgery to create an arterio-venous fistula in the upper or lower arm is planned.

5. Aged over 19 years

6. Treating team agreeable to patient's involvement in the trial and the patient has given informed consent

#### Exclusion criteria include

1. Revision of existing AVF rather than de novo AVF

2. Medical indication for anti-platelet or thrombolytic agents

3. Known intolerance of agents including hypersensitivity to aspirin, allergy to any other NSAIDs or fish

4. Current use of aspirin within two weeks of commencing trial, or of omega-3 fatty acids within 4 weeks of commencing trial

5. Pregnancy, lactation or intention to fall pregnant during the time course of the study

6. Known bleeding disorder or established diagnosis of active or suspected bleeding

7. History of GI ulcers or bleeding within the last 3 months

8. Platelet count less than 100 × 10^9 ^/L

9. Known active peptic ulcer disease

10. Severe hepatic insufficiency

11. Already receiving anti-coagulation therapy such as warfarin

12. Receiving regular non-steroidal anti-inflammatory (NSAIDS) agents for another indication such as arthritis

13. Syndrome of asthma, rhinitis and nasal polyps if uncontrolled on usual therapy

14. Plan to have other (non-access) surgery within 2 weeks of trial medication period where in the opinion of the investigator aspirin or omega-3 fatty acids would be contraindicated for the planned procedure.

15. Potential non-compliance with treatment regimen in the view of the treating clinicians

16. Involved in another clinical trial where the intervention being trialled is likely to confound the outcome of this trial

17. Previously randomised to this trial.

### Outcome measures

The **primary outcome measure **is (unassisted) patency of the AVF at three months after randomisation. This is defined as the presence of an audible bruit throughout systole and diastole over the site of the arterio-venous anastomosis, without the need for surgical or radiological intervention from the time of creation until the time of assessment. The assessment of patency will be made at this time even if the AVF is not yet used for haemodialysis[11].

#### Secondary outcome measures

1. Functional patency at 6 months. This is defined as the ability to use the AVF for dialysis to the satisfaction of the clinician(s), without the need to use alternative dialysis access, or to delay commencement of dialysis due to access unsuitability.

2. Functional patency at 12 months. This is defined as for the outcome measure functional patency at 6 month but is intended to capture the results of patients whose commencement of dialysis is delayed beyond 6 months. In patients who have not needed to start dialysis, assessment of functional patency will be delayed until commencement of dialysis.

3. Time to failure of primary patency: Time from AVF creation to need for first intervention. An event is defined as revision surgery, need for alternative access, or abandonment of AVF whichever comes first. Censored observations are defined as regaining renal function such that dialysis is not needed or still having a patent AVF at time of study analysis. There will be a minimum of 12 months follow up time for each patient.

4. Time to failure of assisted patency. This is defined as time from AVF creation to abandonment of access. That is, radiological and surgical interventions to preserve or restore patency do not constitute failure. An event is defined as abandonment of the AVF as dialysis access. Censored observations will be as for time to failure of primary patency above.

5. Adverse events. All serious adverse events will be collected. The analysis of this secondary outcome will focus particularly on bleeding events.

**Exploratory outcome measures **are also defined, in order to confirm the validity of the primary outcome measure, and to provide a means of comparison with other previous trials:

1. Patency in the first 24 hours post surgery: determined by the presence or absence of a bruit over the site of the anastomosis, with standard stethoscope.

2. Patency at 6 weeks post surgery: determined by the presence or absence of a bruit over the site of the anastomosis.

3. Time to first cannulation of the AVF: time taken as time of surgery until the first attempt at access cannulation.

4. Time to consistent cannulation of the AVF: time taken as the time from surgery until that of the 3rd consecutive dialysis session with successful cannulation of the access.

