### Treatment plan and modifications

The study treatment commences on the day prior to the scheduled AVF surgery and will continue for 3 months. Participants will take 100 mg of Aspirin per day p.o. or matching placebo and 4 g of omega-3 fatty acids in divided doses (2 g twice daily) in the form of Omacor capsules, 45% eicosapentaenoic acid (EPA) and 45% docosapentaenoic acid (DHA), or matching placebo.

Compliance will be monitored by capsule/tablet count at scheduled study visits at week 1, 6 and 12. Selected centres will also measure erythrocyte fatty acids for compliance with omega-3 fatty acid intake and urinary thromboxane B2 levels (for patients with urine output) for compliance with aspirin intake. Centres will apply routine biochemistry (lipids, CRP) and haematology analyses as part of patient monitoring.

Study treatment may be discontinued if one of the following occurs:

1. A major bleeding event (e.g. haemorrhagic stroke, gastro-intestinal bleed);

2. The access is abandoned due to thrombosis at any time after the one week assessment;

3. An AVG rather than an AVF is created, or a vein graft is used;

4. Anti platelet therapy or anticoagulation is indicated because of other co morbid events i.e. for example a major cardiovascular event;

5. A female patient becomes pregnant while on study medication. The event should be reported to the trial coordinating centre immediately as a medically important SAE. The event will be reported to Bayer Safety within 24 hours by the coordinating centre and follow up performed through to delivery;

6. The AV anastomosis is created in the lower limbs rather the upper limbs during surgery.

7. Patient receives renal transplant

Study treatment should be continued if:

1. Further access is created (including a new AVF or AVG, peritoneal and venous catheter) because of failure of maturation of the study AVF, i.e. access is still patent;

2. Renal function is recovered; the study AVF can still be measured for patency.

No other anti-platelet or anti-coagulation agent will be permitted during the period the patient is taking study medication.

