### Statistical Considerations

#### Sample size calculation for the primary outcome

The event rate for the primary outcome (failure of primary patency) is estimated to be 25% at three months in the control group. If a 30% relative risk reduction is achievable with either aspirin or omega-3 fatty acids, then with 80% power and a significance level of 5%, 1200 study subjects will be required (300 receiving double placebo, 300 active aspirin and placebo omega-3 fatty acids, 300 active omega-3 fatty acids and placebo aspirin, and 300 both active aspirin and active omega-3 fatty acids in a factorial design). This allows for 5% drop-in from placebo to active treatment (either aspirin or omega-3 fatty acids), 5% drop-out from study treatment (to no treatment – assumed equivalent to placebo), and 5% loss to follow-up. This is equivalent to an observed relative risk reduction of 24%. Without adjustment for compliance, the study size needed would have been 932 subjects.

The study is not adequately powered to detect a clinically important difference between the combination of aspirin and omega-3 fatty acids and either treatment alone, but preliminary data on the combination will be obtained. The event rate of the primary outcome, primary failure, is based on review of all papers published in this area. The effect size, a 30% reduction, is based on the smallest size of the effect the proposing clinicians believe would lead to a change in practice (incorporation of intervention) should the trial prove the intervention is efficacious.

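### The event list for time to failure of primary patency omits radiological intervention and does not tie alternative access to failure of the study fistula

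*Protocol article*

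**What the plan says.** All places are in the protocol article.

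- **Secondary outcome measures, item 3, opening sentence:** "Time to failure of primary patency: Time from AVF creation to need for first intervention". The type of intervention is not restricted.
- **Item 3, event rule:** "An event is defined as revision surgery, need for alternative access, or abandonment of AVF whichever comes first".
- **Item 3, censoring rule:** "Censored observations are defined as regaining renal function such that dialysis is not needed or still having a patent AVF at time of study analysis".
- **Item 4 (assisted patency):** "radiological and surgical interventions to preserve or restore patency do not constitute failure". Only abandonment of the fistula is an event there, and censoring follows item 3.
- **Outcome measures (primary outcome):** unassisted patency requires a bruit "without the need for surgical or radiological intervention from the time of creation until the time of assessment". Use for dialysis is not required: "The assessment of patency will be made at this time even if the AVF is not yet used for haemodialysis".
- **Sample size calculation for the primary outcome:** the same term is applied here to the three-month endpoint: "The event rate for the primary outcome (failure of primary patency) is estimated to be 25% at three months in the control group".
- **Treatment plan and modifications:** study treatment continues if further access is created "because of failure of maturation of the study AVF, i.e. access is still patent".

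**The concern.** Primary and assisted patency differ in one respect: whether a procedure that keeps the fistula open counts as failure. Item 4 names two kinds of procedure that assisted patency tolerates, radiological and surgical. Item 3 should therefore count both as failure, and its opening sentence suggests that it does. The event rule then lists only the surgical kind.

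The same rule also adds a component that the primary outcome does not have, the need for another access, and does not say that this need must come from failure of the study fistula. The treatment section describes a situation in which it does not.

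What is at stake is whether the time-to-event result measures primary patency as the trial defines it elsewhere. The two faults work in opposite directions on the event count. The first drops events or dates them late. The second may add events in patients whose fistula is patent and has had no intervention. Two people coding the same record could also reach different answers, because the opening sentence, the event rule and the censoring rule do not agree.

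**Working it through.** No figure in the protocol is derived from the item 3 event rule, so there is nothing to recompute. The sample size for the primary outcome rests on the three-month proportion (25% in controls, and 25% × 0.70 = 17.5% under the assumed 30% relative reduction) and does not use item 3. The check is therefore to apply each definition to the same patients.

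| Patient | Primary outcome at three months | Item 3, opening sentence | Item 3, event rule | Item 3, censoring rule | Item 4 |
|---|---|---|---|---|---|
| A. Radiological procedure before three months; fistula patent thereafter | Failed | Event at the procedure | No event | Censored as patent | No event |
| B. Radiological procedure first, surgical revision later | Failed if either falls before the assessment | Event at the radiological procedure | Event at the later surgery | Does not apply | No event |
| C. Surgical revision only; fistula patent thereafter | Failed if before the assessment | Event at surgery | Event at surgery | Wording also fits, but the event comes first | No event |
| D. Slow maturation, another access created; study fistula patent with no intervention on it | Patent | No intervention on the fistula, so no clear event | Event | Also fits: still patent at analysis | No event |

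**Patients A and B (omission).** Patient A has failed the primary outcome and has had a first intervention, yet meets none of the three listed events. The censoring rule then classes the patient as still patent. The radiologically treated fistula is unfailed in both item 3 and item 4, so the two outcomes no longer differ for this patient. Patient B has an event, but at the date of the second procedure instead of the first.

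**Patient C (control case).** Surgical intervention is handled consistently: it ends primary patency in every definition and is tolerated in item 4. The gap is specific to radiological procedures.

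**Patient D (alternative access).** The treatment section describes this patient and calls the fistula patent. The primary outcome also calls it patent, because use for dialysis is not required. The event rule read literally gives an event, while the censoring rule read literally also fits. The text does not say which prevails, nor whether slow maturation with a patent fistula is meant to be failure of primary patency.

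**Size.** Two rates would be needed: the share of first interventions that are radiological, and the share of participants who need other access while the study fistula is patent. The protocol gives neither, and nothing in it supports a plausible range.

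**The case against.** The best reply on radiological intervention is that the intention can be recovered. The opening sentence covers any first intervention, item 4 draws the contrast explicitly, and the event list can be read as an incomplete elaboration. That is a fair account of what was probably meant, and it is why the repair is simple. It does not remove the fault: the sentence that formally defines the event is the list, and on the generous reading it contradicts the sentence before it.

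On alternative access, it can be argued that counting a fistula that has to be replaced as failed is a legitimate choice for an outcome with at least 12 months of follow-up, and that it need not copy the three-month definition. That stands as far as it goes. A difference from the primary outcome is not in itself an error. What remains is that the rule does not say whether access created beside a patent fistula counts, and that the censoring rule points the other way.

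It can also be said that the trial is double-blind, so coding should not depend on allocation. That lowers the risk of biased coding. It does not make the outcome measure what its name says.

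Three stronger readings are tempting and are not supported:

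- A reader might infer that patients dialysing through a catheter placed before surgery have an event at day 0. Item 3 runs from fistula creation to a need that arises afterwards, so access already in place is not naturally such an event.
- A reader might infer from the Background that up to half of participants would be affected, since half of new patients start haemodialysis with a catheter. That statement attributes the catheter to a failed or inadequate fistula and describes new patients in the two countries, not trial participants. The trial also admits patients whose haemodialysis is only planned and patients on peritoneal dialysis.
- A reader might count the silence on death and transplant in the censoring rule as a further fault. Such detail is commonly left to the full protocol or the analysis plan, neither of which is shown.

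**Conclusion.** The point holds in two parts. First, the item 3 event rule omits radiological intervention and so conflicts with its own opening sentence, with item 4 and with the primary outcome definition. A fistula kept open by a radiological procedure alone is censored as patent although it has failed primary patency as the trial defines it. This rests on the wording alone and needs no assumption. Second, alternative access is not tied to failure of the study fistula, so a patient with a patent fistula and a further access fits both the event and the censoring wording.

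The reach is limited. One secondary time-to-event outcome is affected. The primary outcome, its chi-square analysis and the sample-size calculations for the primary outcome and for six-month patency do not depend on it. The number of patients misclassified, and the effect on the treatment comparison, cannot be computed from the protocol. The text supports saying that the outcome is inconsistently defined. It does not support saying that the result would be invalid or biased by a particular amount.

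**What to change.** Rewrite the item 3 event as the earliest of:

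- the first surgical or radiological intervention on the study fistula to maintain or regain its patency;
- abandonment of the study fistula;
- alternative access, but only when it is newly needed after fistula creation because the study fistula has failed.

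If the sponsor prefers a different rule for the third component, the text should state outright whether access created while the study fistula is patent, including for slow maturation, is or is not an event. The censoring rule should then be aligned so that no patient fits both, for example by limiting censoring for a patent fistula to patients with no earlier event. Item 4 takes its censoring from item 3 and should be reread after the change.

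The cost is small: revised wording, and a check that the data form captures the date and type of each intervention. Table 1 lists only the description and status of the fistula at each visit, so it does not show that this is already recorded. The article says the trial has been launched. If the form lacks these items, they would have to be collected for patients already enrolled, and the definition should be settled before treatment allocation is unblinded.

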### Study Procedures

Participants will be recruited from public and private hospital renal units providing haemodialysis and vascular access services in Australia and New Zealand. Patients will meet the inclusion and exclusion criteria and be scheduled to undergo surgery for creation of a de novo AV fistula. Processes to identify and screen all potential recruits will be established within each centre with consultation with the Trial Management Committee.

Patient consent forms will be approved by the Human Research Ethics Committee at each participating site prior to the beginning of the trial. A sample consent form and patient information sheet is provided to participating sites. Participating sites will file a copy of the approved consent form and information sheet for their site with the coordinating office. After discussing the trial, ample time will be given to the participant, accompanying person or legal representative to inquire about the trial and decide whether to participate. No person involved with the trial will coerce or unduly influence the decision of a patient to participate in a trial. A copy of the signed consent form and the patient information sheet will be supplied to the participant. Patient consent must be obtained prior to the registration or initiation of trial procedures. Patients will not be randomised until a signed consent form is filed at site and notification is received by the coordinating office.

The Trial Management Committee will monitor the medical literature, and any other relevant information impacting on the continuation of the trial. Consent forms and patient information sheets will be revised should any relevant and important new information become available.

Registration will occur when subjects come for their surgical consultation prior to the operation to create the AVF. The patient will have an initial consultation with a study renal physician or surgeon to discuss study participation. This will include a preliminary eligibility check. Consenting patients will be registered by emailing or faxing a completed registration form to the coordinating centre. The registration form also serves as notification of completion of a patient consent form. The patient will also be randomised at this time. Stratification will occur for study site, incident versus prevalent patient status and upper vs. lower arm site. Patients will be randomised to one of four treatment groups in equal proportion.

Please refer to table 1 for an outline of the timing of the study visits study assessments preformed at those visits.

**Table 1 T1:** Outline of Favoured Study Procedures

Study Visits	Baseline	Randomisation	Surgery	Treatment Period (wks)			Follow-up (mths)					
**Assessment**	**≤ 4 wks prior to surgery**	**≤ 7 Days prior to surgery**		**1**	**6**	**12**	**6**	**12**	**18**	**24**	**30**	**36**

Informed Consent	X											
Study Medication Allocated		X										
Medical History and Physical Exam	X											
Weight & Blood Pressure	X		X	X	X	X	X	X	X	X	X	X
Demographics	X											
Dialysis status	X			X	X	X	X	X	X	X	X	X
Description and status of AVF			X	X	X	X	X	X	X	X	X	X
Concomitant meds	X		X	X	X	X	X					
Adverse events			X	X	X	X	X					
Routine fasting blood & urine samples	X					X						
Batched blood & urine samples	X				X	X						

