**Methods/Design:**

The study population is adult patients with stage IV or V chronic kidney disease (CKD) currently on HD or where HD is planned to start within 6 months in whom a planned upper or lower arm AVF is to be the primary HD access. Using a factorial-design trial, patients will be randomised to aspirin or matching placebo, and also to omega-3 fatty acids or matching placebo, resulting in four treatment groups (aspirin placebo/omega-3 fatty acid placebo, aspirin/omega-3 fatty acid placebo, aspirin placebo/omega-3 fatty acid, aspirin/omega-3 fatty acid). Randomisation will be achieved using a dynamic balancing method over the two stratification factors of study site and upper versus lower arm AVF. The medication will be commenced pre-operatively and continued for 3 months post surgery. The primary outcome is patency of the AVF at three months after randomisation. Secondary outcome measures will include functional patency at six and twelve months, primary patency time, secondary (assisted) patency time, and adverse events, particularly bleeding.

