### Analysis

Analysis of the primary outcome (patency) will be on an intent-to-treat basis. All randomised patients will be analysed in the group they were allocated to, even if they do not receive treatment as allocated, or do not commence treatment. All randomised patients will be included in the analysis.

The primary outcome is measured as the proportion with failure of patency at three months after randomisation. The primary hypothesis will be tested using a chi-square test of proportions to test the null hypotheses that a) the proportion of failures in those allocated to aspirin versus those allocated to placebo aspirin is equal, and b) the proportion of failures in those allocated to omega-3 fatty acids versus those allocated to placebo omega-3 fatty acids is equal. The primary outcome will be measured at 84 days after randomisation, with a permitted tolerance of 7 days prior, and 14 days after the due date of 84 days. Tests of hypotheses will be at the 5% significance level, and 2-sided p-values will be used.

Any patient who does not have a 84-day measure will be counted as failure of patency in the primary analysis. A secondary analysis will be done including only those with a 84-day measure to test the sensitivity of the analysis of the main treatment comparisons to patient exclusions. As this is a short-term intervention, with a relatively short recruitment period, the only planned interim analysis is of safety. This will be conducted at 1/3 and 2/3 of total patient numbers accrued. Similar analyses to the primary one will be undertaken on the secondary outcomes, as well as exploratory analyses looking at the validity of the chosen primary outcome and its correlation with other outcomes, and the prediction of thrombosis from baseline variables such as markers of inflammation.

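### The protocol lists two balancing factors in two places and three in another, and the primary chi-square test uses none of them, which forgoes a little power if they are prognostic

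*Protocol article*

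**What the plan says.** The balancing factors are stated three times.

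- Abstract, Methods/Design: a "dynamic balancing method over the two stratification factors of study site and upper versus lower arm AVF".
- Study Design: "balancing over the two stratification factors of 1) study site and 2) upper versus lower arm AVF".
- Study Procedures: "Stratification will occur for study site, incident versus prevalent patient status and upper vs. lower arm site".

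The first two agree on two factors. The third adds incident versus prevalent status. Study Procedures also sets the allocation ratio: "Patients will be randomised to one of four treatment groups in equal proportion".

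For the primary outcome, the Analysis section says: "The primary hypothesis will be tested using a chi-square test of proportions". One test compares aspirin with its placebo and one compares omega-3 fatty acids with its placebo. On the level: "Tests of hypotheses will be at the 5% significance level, and 2-sided p-values will be used". No balancing factor enters either test. The section intends similar analyses for the secondary outcomes, so the choice carries over to them.

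**The concern.** Two separate things are at stake.

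The first is the description of the trial. An allocation program balances over two factors or over three, not both. If it was built to Study Design, then Study Procedures is wrong. If it was built to Study Procedures, then the Abstract and Study Design are wrong. The report's account of the randomisation, and the covariates of any analysis that adjusts for the balancing factors, depend on which list is true.

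The second is efficiency. Balancing on a factor that predicts failure removes part of the chance difference between arms. The ordinary chi-square test does not know this and computes its variance as if allocation had been simple. Its standard error is then somewhat too large and its true type I error falls below 5%. It gives up power that an adjusted analysis would recover from the same data. The protocol gives some reason to think site may matter. The Background names better surgical technique as a way to lower primary failure, and the Discussion offers surgical volume and nursing skill as possible reasons for high functional failure elsewhere. Neither statement quantifies a site effect on three-month patency.

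**Working it through.** **1. The factor lists side by side**

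| Place | Site | Upper vs lower arm | Incident vs prevalent |
|---|---|---|---|
| Abstract | yes | yes | no |
| Study Design | yes | yes | no |
| Study Procedures | yes | yes | yes |

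Study Design counts and numbers its factors, so its list cannot be read as a partial one.

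**2. What the stated sample size assumes**

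The primary failure rate "is estimated to be 25% at three months in the control group". A 30% relative reduction gives 0.25 × 0.70 = 0.175. For two proportions with pooled variance under the null, two-sided 5%, 80% power and no covariates:

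n per margin = [1.96·√(2·0.2125·0.7875) + 0.8416·√(0.25·0.75 + 0.175·0.825)]² / 0.075² = 466, so the total is 932.

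This is exactly the protocol's unadjusted figure. With 5% drop-in and 5% drop-out the rates become 0.25 − 0.05·0.075 = 0.24625 and 0.175 + 0.05·0.075 = 0.17875. The requirement is then 576 per margin, 1,152 in total, and 1,152/0.95 = 1,213, against the stated 1,200. With 1,200 × 0.95 / 2 = 570 evaluable per margin, power is 79.6%. The stated power is therefore that of an unadjusted comparison.

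The section also equates this with an observed reduction of 24%, whereas 1 − 0.17875/0.24625 = 27.4%. That is a separate matter. It does not affect the type I error figures below, although a smaller reduction would lower both power columns.

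**3. Effect of ignoring balanced factors**

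Let R² be the share of outcome variance that the balanced factors explain. With good balance, the variance of the treatment difference is (1 − R²) times what the chi-square assumes. Write f = √(1 − R²), d = 0.0675, and se₀ = 0.02423 and se₁ = 0.02415 for the standard errors under null and alternative with 570 per margin.

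- Type I error of the chi-square = 2·[1 − Φ(1.96/f)]
- Power, unadjusted = Φ[(d − 1.96·se₀)/(f·se₁)]
- Power, adjusted = Φ[(d − 1.96·f·se₀)/(f·se₁)]

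| Assumed R² | Type I error, chi-square | Power, unadjusted | Power, adjusted | Difference (points, before rounding) |
|---|---|---|---|---|
| 0 | 5.0% | 79.6% | 79.6% | 0.0 |
| 0.02 | 4.8% | 79.9% | 80.4% | 0.6 |
| 0.05 | 4.4% | 80.2% | 81.6% | 1.4 |
| 0.10 | 3.9% | 80.9% | 83.6% | 2.8 |

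As a guide, with half the fistulas at each arm site, R² is about 0.02 for a between-site SD of 0.3 on the logit scale and an arm odds ratio of 1.5. It is about 0.06 for SD 0.5 and odds ratio 2, and about 0.12 for SD 0.8 and odds ratio 2.5. All of these strengths are assumptions.

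**4. Simulation under dynamic balancing**

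Set-up: four groups, 1,140 evaluable patients, 30 sites (assumed), 5,000 runs per cell. Weak, moderate and strong are the three settings above. Where incident status is the third factor, its odds ratios are 1.3, 1.5 and 2. The main-effects analysis was a linear model with site and factor indicators. Monte Carlo error is about 0.3 points for type I error and 0.6 for power.

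| Factors | Type I: chi-square / Mantel-Haenszel / main effects | Power: chi-square / Mantel-Haenszel / main effects |
|---|---|---|
| Two, none prognostic | 5.0 / 4.8 / 4.8% | 79.6 / 78.6 / 79.7% |
| Two, weak | 4.5 / 4.9 / 4.7% | 80.5 / 80.0 / 81.2% |
| Three, weak | 5.0 / 5.4 / 5.3% | 79.2 / 76.1 / 80.0% |
| Two, moderate | 4.5 / 5.0 / 4.9% | 80.8 / 80.6 / 82.1% |
| Three, moderate | 4.2 / 4.6 / 4.7% | 80.3 / 78.3 / 82.1% |
| Two, strong | 3.4 / 4.5 / 4.6% | 80.5 / 82.1 / 83.0% |
| Three, strong | 4.0 / 5.2 / 5.1% | 81.3 / 81.0 / 83.8% |

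Main-effects adjustment gains 0.1 to 2.5 points. Mantel-Haenszel over every site-by-factor cell has less power than the plain chi-square in six of the seven settings. The reason is sparse strata: 30 × 2 × 2 = 120 cells hold on average 1,140/120 = 9.5 patients each.

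**The case against.** The strongest reply concerns the analysis. An unadjusted primary test is permissible, simple and valid here, because its type I error does not exceed 5% on this account. The trial was sized for that test, and simulated power stays at about 79% or above in every setting. The conservatism depends on prognostic strength that the protocol never states, and with weak factors the simulation can hardly tell it from 5%. An analysis plan not shown here may add an adjusted analysis. Adjustment is also not automatically better, since full cross-stratification can cost more power than it recovers. A logistic model would move the effect from proportions to a conditional odds ratio.

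All of this stands. It limits the analysis point to a conditional and modest gain forgone, and it determines the form of the remedy. It does not remove the point, because the Analysis section itself fixes the chi-square as the primary test, and a main-effects adjustment did not lose power in any setting examined.

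A reader might also infer that each drug's comparison is wrong because it ignores allocation to the other drug. The documents do not support that. Equal allocation to four groups makes the two factors orthogonal by design, and comparing the margins matches the stated null hypotheses.

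None of these replies touches the contradiction in the factor list.

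**Conclusion.** The contradiction is certain: two factors in the Abstract and Study Design, three in Study Procedures. The documents do not show which list the randomisation system uses, so it would go too far to infer that the allocation itself has gone wrong.

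The analysis point is real but small and conditional. For an assumed R² of 0.02 to 0.10, the unadjusted chi-square has a true type I error of about 4.8% to 3.9% and forgoes about 0.5 to 3 points of power. With R² = 0 there is no effect. These figures rest on assumed prognostic strengths, on the stated 5% drop-in, drop-out and loss, and, in the simulation, on 30 sites.

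Two stronger readings should be resisted. One is that the primary test is invalid; any departure from 5% on this account is downwards. The other is that the planned 80% power is eroded; it was computed for an unadjusted comparison, and balancing on prognostic factors slightly raises that test's power.

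**What to change.** 1. Confirm from the randomisation system which factors it balances over, and state that single list in the Abstract, Study Design and Study Procedures.
2. Before unblinding, replace the primary test in the Analysis section with one adjusted for those factors as main effects, such as a logistic model. Treat site as a random effect, or pool small sites by a rule fixed in advance. Do not use a Mantel-Haenszel test over all site-by-factor cells.
3. Report a marginal risk difference or relative risk from that model, so that the effect stays on the scale of proportions used for the sample size and the hypotheses.
4. Keep the unadjusted chi-square as a sensitivity analysis. Adjusting for the other drug's allocation is optional.

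The cost is a sentence in each of three places and a short paragraph in the Analysis section. No extra patients are needed and no new data, since the balancing factors must be known at randomisation. The recommended random-effect or pooled-site model was not itself simulated; the gains shown come from a linear model with site indicators.
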